### Control condition

Participants who are allocated to the control arm will continue to receive their usual care. Treatment as usual for the participants in this trial will typically consist of monitoring meetings with a general practitioner or mental health practitioner and psychiatric medication (as needed). Treatment as usual will vary across individuals, clinical teams and mental health trusts. We will collect detailed data on treatment as usual (which will also inform the preliminary health economic evaluation).

At the end of their participation in the study, participants in the control arm will be offered a one-off session about sleep with a clinical psychologist. This session will briefly identify a plan to improve sleep, which participants may then implement independently. The LEAP emphasised the importance of offering this session.

### Adverse events

A serious adverse event (SAE) is defined as any untoward medical occurrence that results in death, is life threatening, requires or prolongs hospitalisation or results in persistent or significant disability/incapacity. The sorts of SAEs that can typically occur in this participant group include: deaths, suicide attempts, serious violent incidents, and admissions to hospital. Hospitalisation for a pre-existing physical health condition, including elective procedures planned prior to study entry, which has not worsened, does not constitute an SAE.

A trial standard operational procedure has been written for adverse events. We will record the occurrence of any SAEs reported to us and also systematically check all participants’ medical records following completion of the final assessment. We will also record transition to psychosis and formal complaints regarding therapy. Transition to psychosis will be determined through multiple sources including: scoring above psychosis threshold on the CAARMS^30^ at the research assessments; review of medical records; clinical team feedback; prescription of anti-psychotic medication, and the clinical observation of the study therapist. The responsible clinical team, the trial management committee and the DMEC will be informed of any adverse event.

### Analysis

A full statistical analysis plan will be drafted prior to recruitment beginning and finalised before any analysis takes place. There are no interim analyses or formal stopping rules in relation to this study as the primary goal is to establish feasibility parameters for a definitive trial. Data will be reported in line with the CONSORT 2010 Statement, SPIRIT and GRIPP2 guidelines.

Analysis will be descriptive in nature and no hypothesis testing will be carried out. The number (percentage) will be presented for feasibility measures (ie, recruitment and retention, uptake of treatment, data completion) overall and by randomised group. Progression criteria related to key feasibility outcomes such as recruitment, retention, and treatment uptake rates have been identified. These criteria outline the potential progression from feasibility to definitive trial. Each criterion has ‘stop/amend/go’ indicators. For example, the progression criterion for treatment uptake will be: 75% and above indicates the progression criterion has been met, 51% to 75% indicates the need to amend, and below 50% indicates stop.

The patient outcome measures will be described using the mean (SD) or median (IQR) depending on the distribution of the measure and by the number (percentage) for binary outcomes. At baseline, patient measures will be reported overall and by randomised group. At follow-up points, patient outcomes will be presented by randomised group and the difference between groups and 95% CI for the difference will be reported to aid sample size calculations for the definitive trial.

The primary aim of this feasibility trial is to establish the necessary parameters for a definitive trial. This includes recruitment, retention, and treatment uptake rates. A sample size of 20 per randomised group (40, in total across the study) will be sufficient to estimate a recruitment rate of 50% with a 95% CI of 35% to 65% and a retention rate of 80% with a 95% CI of 65% to 90% (PASS V.12). This sample size of 20 per arm will be sufficient to estimate the variability of outcome measures for future sample size calculations, with 12 per arm sufficient for estimation of the variability for the purpose of sample size calculations.^56^

All participants recruited to the feasibility trial will be documented fully with respect to receiving the intervention and participating in follow-up. Although no formal statistical analysis will be undertaken, outcomes will be reported by randomised group for all participants randomised, irrespective of whether they received the intervention or not (intention-to-treat). Adverse events will be reported for all participants randomised.

A microcosting approach will be used to inform the cost per patient of the SleepWell intervention. As part of this feasibility study, we will determine the acceptability and completeness of the necessary data (CSRI, medication use, ReQOL and EQ-5D) to perform a full health economic analysis. Further to this we will investigate the possibility of developing a decision-analytical model that would permit the generation of cost-effectiveness estimates in the long-term (eg, costs and outcomes in patient’s lifetime) based on a large evaluation trial of the SleepWell intervention.

The qualitative interviews will be recorded, transcribed verbatim, and analysed using Thematic Analysis.^57^ This includes the identification of codes, candidate themes and thematic map. A thematic map reflects the meanings of the overall data set and provides a conceptualisation of the themes and relationships between them. Quality guidelines^58 59^ will be followed, including credibility checks and reflexive practice.

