### Randomisation, blinding and code-breaking

Participants will be randomised once they have completed the baseline assessment. Participants will be allocated to one of the trial arms using a 1:1 allocation ratio. Randomisation will be carried out by a validated online system, Sortition, designed by the University of Oxford Primary Care Clinical Trials Unit. Allocation will be carried out using a non-deterministic minimisation algorithm to ensure balance across groups with respect to severity of sleep disturbance (Insomnia Severity Index (ISI) score ≤21/≥22) and referring service (early intervention in psychosis team (EIP), child and adolescent mental health services (CAMHS), improving access to talking therapies service (IAPT)).

The research assessor will be blinded to group allocation, but the patients and clinician delivering the intervention will not be (they cannot be blinded to whether a psychological intervention is delivered or received). If an allocation is revealed between assessment sessions, this is logged by the trial coordinator and future assessments conducted, where possible, by another assessor to re-establish the blind.

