The intervention is delivered by a clinical psychologist, on an individual basis in up to eight 1-hour sessions. There is typically one session per week. Additional contact between sessions (eg, text messages, email) is provided to support treatment strategy implementation. A treatment dose is defined as four or more sessions. In line with the International Early Psychosis Association recommendations that interventions are provided flexibly and in low stigmatising environments, sessions are held in the patient’s home or local health service clinic.^54^ At the final session, participants will be asked to complete a self-report questionnaire to assess the acceptability of the intervention (AARP^55^).

SleepWell will be provided in addition to usual care. With patient consent, sessions will be audio-recorded and independently rated for quality, including fidelity and competence.

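### The stop/amend/go bands for treatment uptake overlap at exactly 75% and leave 50% to under 51% without a verdict, and both points can occur with 20 intervention patients

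*Protocol article*

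**What the plan says.** The Analysis section says that progression criteria exist for the key feasibility outcomes, naming recruitment, retention and treatment uptake, and that "Each criterion has ‘stop/amend/go’ indicators". Treatment uptake is given as the example and is the only criterion whose bands appear: "75% and above indicates the progression criterion has been met, 51% to 75% indicates the need to amend, and below 50% indicates stop".

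The same section plans "A sample size of 20 per randomised group (40, in total across the study"), and the section on randomisation states: "Participants will be allocated to one of the trial arms using a 1:1 allocation ratio". The article gives no rounding rule or tie-break and does not restate the bands elsewhere.

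**The concern.** A three-way rule should assign each possible result to one category. Here the value 75% satisfies the wording of two categories, and the values from 50% up to but not including 51% satisfy none. This is a fault in text that the article states, not a detail it leaves to the analysis plan.

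The decision about a definitive trial would be affected. If uptake lands on one of these points, someone must choose between go and amend (at 75%) or between amend and stop (at 50%) with the result already known. Progression criteria are fixed in advance to avoid that choice.

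**Working it through.** **Inputs.** The bands come from the Analysis section. The denominator is taken as 20, the planned size of the SleepWell arm, because only that arm is offered the intervention (The SleepWell intervention; Control condition). The true uptake rates below are assumptions, since the article states no expected uptake.

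**The plan's own figures.** The bands carry no precision or power figure. The nearest stated figures are the 95% intervals for recruitment and retention, and these reproduce with n = 40 and the Wilson score interval, (p + z²/2n ± z√[p(1−p)/n + z²/4n²]) / (1 + z²/n), z = 1.96:

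- p = 0.50: 35.2% to 64.8% (stated 35% to 65%).
- p = 0.80: 65.2% to 89.5% (stated 65% to 90%).

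The sample-size statement is therefore not in question.

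**Step 1: enumerate the results.** With 20 patients, uptake moves in steps of 1/20 = 5 percentage points.

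| Patients with uptake | Percentage | Verdict as written |
|---|---|---|
| 0–9 | 0–45% | stop |
| 10 | 50% | none |
| 11–14 | 55–70% | amend |
| 15 | 75% | go and amend |
| 16–20 | 80–100% | go |

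Of 21 possible counts, 19 get exactly one verdict. Reading the bands as whole percentages does not help: the gap shrinks to the single value 50%, and 10/20 is exactly that value.

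**Step 2: chance of each faulty result.** P(X = x) = C(20, x) pˣ (1−p)²⁰⁻ˣ. Two examples:

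- P(10) at p = 0.50: 184,756 × 0.5²⁰ = 0.176.
- P(15) at p = 0.75: 15,504 × 0.75¹⁵ × 0.25⁵ = 0.202.

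| Assumed true uptake | P(10/20), no verdict | P(15/20), two verdicts |
|---|---|---|
| 50% | 17.6% | 1.5% |
| 60% | 11.7% | 7.5% |
| 70% | 3.1% | 17.9% |
| 75% | 1.0% | 20.2% |
| 80% | 0.2% | 17.5% |
| 85% | under 0.1% | 10.3% |
| 90% | under 0.1% | 3.2% |

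**Step 3: other arm sizes.** Allocation is by minimisation with a random element, so the arm need not be exactly 20. Repeating step 1:

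- 17, 19, 21 or 23 patients: neither faulty value can occur. With 19, for example, the results nearest the two points are 9/19 = 47.4%, 10/19 = 52.6%, 14/19 = 73.7% and 15/19 = 78.9%.
- 18 or 22 patients: only 50% can occur.
- 16 or 24 patients: both can occur.

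**The case against.** The best defence is that little depends on the boundary. The bands are given as an example, are described as indicators, and concern a possible rather than automatic move to a definitive trial. The section plans no formal stopping rule and no hypothesis test. The uptake count and percentage will be reported whatever label is attached, and uptake is one of at least three criteria. All of this stands, and it limits the severity.

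The overlap at 75% is also the milder half. The go wording has no upper limit or condition, so many readers would take 15/20 as go. Only 50% has no verdict at all. This stands too, and it is why the two probabilities are shown separately.

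Some stronger readings are tempting but not supported:

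- *The rule fails about one time in five.* Adding the two columns gives 17.7% to 21.2% for true uptake between 50% and 80%. That sum merges two unequal faults, assumes exactly 20 in the arm, and ends at 80%; it falls to about 10% at 85% and 3% at 90%. The article gives no expected uptake. Its nearest figure, 89% attendance in the earlier case series (Rationale), is a different measure.
- *Pre-specification loses its value.* Nineteen of 21 results are unambiguous, and each faulty one lies between neighbouring verdicts. Moreover, the Objectives section gives the aim as establishing parameters for a definitive trial, which is broader than a single go decision.
- *Uptake is undefined, or the other criteria share the fault.* The article says "A treatment dose is defined as four or more sessions" but does not tie this to uptake. That definition, like the recruitment and retention bands, may properly sit in the full protocol or analysis plan, and nothing here shows either to be wrong.

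**Conclusion.** The point holds. As written, the uptake bands give two verdicts at exactly 75% and none from 50% to under 51%, and the planned arm of 20 can land on both points. Under assumed true rates, the missing verdict is a real possibility if uptake is near 50% to 60% (17.6% to 11.7%) and negligible from 80% upwards. The double verdict is most likely near 75% (20.2%) and fades to 3.2% at 90%.

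These probabilities assume 20 patients in the denominator and independent patients with a common uptake rate. The wording fault needs no such assumption.

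Severity is moderate. The feasibility verdict is affected; no estimate or interval is. The full protocol or analysis plan may word the bands correctly, which cannot be checked here. If so, the article should be reconciled with it.

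**What to change.** Before any outcome data are seen, restate the bands so that each possible result gets exactly one verdict. Two versions would do this:

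- Go at 75% or more, amend at 50% to under 75%, stop below 50%. This keeps the stated go and stop wording and changes only the middle band. With 20 patients: 15–20 go, 10–14 amend, 0–9 stop.
- Go at 75% or more, amend above 50% and under 75%, stop at 50% or below, if the team meant 50% to be a stop. With 20 patients: 15–20 go, 11–14 amend, 0–10 stop.

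The present text does not settle which was intended, since the stop band excludes 50% while the amend band starts at 51%. The trial team should choose. Percentages without gaps will also work if the arm is not exactly 20.

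The cost is one sentence in the protocol and, if it repeats the bands, in the analysis plan. No patients, visits or procedures change.

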### Objectives

We aim to assess the feasibility of a targeted intervention to improve sleep and prevent psychosis in young people at ultra-high-risk of psychosis.

The primary objective is to assess the feasibility and acceptability of a targeted sleep intervention to prevent psychosis in young people at ultra-high-risk in order to establish the key parameters for a definitive RCT. The secondary research objective is to gather data on clinical outcomes to provide a preliminary indication of the clinical efficacy of the sleep intervention (SleepWell) for young people attending National Health Service (NHS) mental health services with sleep problems who are at ultra-high-risk of psychosis. Table 1 provides a summary of the objectives (and the associated feasibility markers or assessment measures).

**Table 1 T1:** Summary of objectives and assessment measures

	Objectives	Outcome measures
Primary	Assess the feasibility and acceptability of a targeted sleep intervention to prevent psychosis and to establish key parameters for a future randomised controlled trial.	Number of patients identified, recruited, declined and retained.
		Number of referrals made per site, and per service type, per month.
		Service use as measured on the CSRI.
		Completion rate of each assessment measure, including wearable-technology devices. Time taken to complete each assessment.
		Location and attendance at treatment sessions; content covered in treatment sessions; feedback from qualitative interviews; treatment acceptability score (AARP).
		Service use data completeness, time taken to collect service use data.
Secondary	Gather data on clinical outcomes to provide a preliminary indication of the clinical effectiveness of a novel sleep intervention (SleepWell) in addition to usual care versus usual care alone in young people with sleep problems who are at ultra-high-risk of psychosis attending NHS mental health services	Sleep disturbance: ISI; Sleep-50 CRD; Sleep diary; Actigraphy; Fatigue. Attenuated psychotic experiences: CAARMS; SPEQ-H; R-GPTS; ČEFSA. Psychiatric symptoms: DASS-21; C-SSRS; DWQ; BCSS. Activity and social functioning: Time budget; WASA; Oxford Agoraphobic Avoidance Scale; actigraphy. Physical health: BMI; step-count; BESAA; PHQ15; MAP. Quality of life: QPR; ReQoL; EQ5D. Service use: CSRI; and medication. Participant ranking of clinical outcome variables.

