### Participants

The trial participants will be 40 young people (aged 14 to 25 years) attending NHS mental health services with sleep problems who are at ultra-high-risk of psychosis. The principal method of recruitment will be via seeking referrals from the relevant clinical teams in the participating NHS mental health trusts. The services include specialist early intervention in psychosis services (EIP: ages over 14 years), child and adolescent mental health services (CAMHS: ages 0 to 18 years) and improving access to psychological therapies services (IAPT: ages over 18 years). The study will be advertised within participating NHS trusts and on social media so that young people receiving care in the recruiting NHS trusts can self-initiate referral to the trial. With the approval of the clinical team, all young people interested in taking part will then be approached by the research team, given information about the trial, and the screening conducted. The importance of self-initiated referral was highlighted by our LEAP to ensure accessibility and inclusivity. Informed consent will be obtained from all patients before participation.

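### The 35% to 65% interval for a 50% recruitment rate uses the 40 randomised patients as denominator; with 40 recruited it would be about 39% to 61%, a minor and conservative error

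*Protocol article*

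**What the plan says.** The Analysis section of the protocol article names recruitment, retention and treatment uptake as the parameters the trial is meant to establish, and then justifies its size. The basis is "A sample size of 20 per randomised group (40, in total across the study"), which the article says "will be sufficient to estimate a recruitment rate of 50% with a 95% CI of 35% to 65" per cent, together with "a retention rate of 80% with a 95% CI of 65% to 90" per cent. Both intervals are attributed to the same sample, and PASS is cited as the software.

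Three other places show what the 40 are:

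- Participants: "The trial participants will be 40 young people (aged 14 to 25 years").
- Randomisation, blinding and code-breaking: patients are randomised only after the baseline assessment, and "Participants will be allocated to one of the trial arms using a 1:1 allocation ratio". All 40 have therefore been recruited before they are allocated.
- Table 1 (Objectives), first primary outcome: "Number of patients identified, recruited, declined and retained". Those identified and those who decline are counted as well as those who join.

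The article does not say which group forms the denominator of the recruitment rate, or how large that group is expected to be.

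**The concern.** A recruitment rate given as a percentage is the number recruited divided by some larger group from which they came. The 40 randomised patients are the top of that fraction. Used as the bottom, they would give a rate of 100%, since every one of them was recruited. A rate of 50% with an interval computed on 40 describes 20 recruited out of 40, which is not this trial. For retention, the same 40 are the correct denominator. One sentence thus uses one number in two roles, and only one of them fits.

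Recruitment is the first feasibility parameter named, and the article says it has a stop/amend/go progression criterion. This sentence is the only statement of how precisely the rate will be known. What is at stake is the accuracy of that statement, not the size of the trial.

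**Working it through.** **Inputs.** Total randomised 40, 20 per arm (Analysis; Participants). Assumed recruitment rate 50%, stated 95% CI 35% to 65% (Analysis). Assumed retention rate 80%, stated 95% CI 65% to 90% (Analysis). Intervals are two-sided at 95%, so z = 1.96 and z² = 3.84.

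**Formula.** The Wilson interval for x out of n, with p = x/n, is

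[p + z²/(2n) ± z·√(p(1−p)/n + z²/(4n²))] / (1 + z²/n).

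**Step 1: reproduce the stated figures with n = 40.** The divisor is 1 + 3.84/40 = 1.096.

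- Recruitment, 20/40: the centre is 0.500. The half-width is 1.96 × √(0.00625 + 0.00060)/1.096 = 0.148. The interval is 35.2% to 64.8%, which rounds to the stated 35% to 65%.
- Retention, 32/40: the centre is (0.800 + 0.048)/1.096 = 0.774. The half-width is 1.96 × √(0.00400 + 0.00060)/1.096 = 0.121. The interval is 65.2% to 89.5%, which rounds to the stated 65% to 90%.

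One method with n = 40 therefore gives both printed intervals. Other methods at n = 40 fit less well:

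| Method, n = 40 | 50% | 80% |
|---|---|---|
| Wilson | 35.2 to 64.8 | 65.2 to 89.5 |
| Wald | 34.5 to 65.5 | 67.6 to 92.4 |
| Exact (Clopper–Pearson) | 33.8 to 66.2 | 64.4 to 90.9 |

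For the 50% rate alone, a Wald interval with n of 42 to 44 or an exact interval with n of 46 to 48 would also round to 35% to 65%. None of these is near 80, and the article states no such number.

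**Step 2: the denominator when 40 are recruited.** Denominator = recruited/rate = 40/0.50 = 80.

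**Step 3: the interval for 40/80.** The divisor is 1 + 3.84/80 = 1.048.

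- Wilson: half-width 1.96 × √(0.003125 + 0.000150)/1.048 = 0.107, giving 39.3% to 60.7%.
- Wald: half-width 1.96 × √(0.25/80) = 0.110, giving 39.0% to 61.0%.
- Exact: 38.6% to 61.4%.

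All three are close to 39% to 61%, and all lie inside 35% to 65%. The half-width is about 11 points, against 15 stated.

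**Step 4: retention.** Its denominator is the 40 randomised, so 32/40 and 65% to 90% stand as printed.

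**The case against.** The strongest reply is that the sentence claims only that the sample is sufficient for the stated precision. An interval of 39% to 61% sits inside 35% to 65%, so the promise is kept with room to spare. Nothing downstream is shown to move: the sample size stays at 40, the separate argument that 12 per arm is enough to estimate variability does not use this interval, and the analysis is descriptive. The article gives no thresholds for the recruitment criterion, and nothing indicates that the planning interval enters it. All of this stands, and it is why the point is minor. It does not make the printed interval right, because the text gives it as the result for this sample and not as an outer bound.

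A second reply is that the denominator may be defined in the full protocol or the analysis plan, which are not shown. That is fair, and its absence from the article is not the complaint. Whichever group is used, the 40 recruited are the numerator and 50% implies 80. Reading the rate as patients per month does not help either: Table 1 lists monthly referrals separately, and 50% with a binomial interval is a proportion.

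A reader might be tempted to go further in two ways:

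- *That the plan implies 40 approaches are enough to complete the trial.* The documents do not support this. The article gives no number to be approached, and Table 1 counts those identified and those who decline, so more patients are plainly expected to be identified than recruited.
- *That the retention interval is wrong too, because 50% of 40 leaves only 20 randomised.* The Participants and Analysis sections both fix 40 in the trial, so that scenario is ruled out.

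**Conclusion.** The concern holds as an arithmetic slip in one planning sentence. The stated 35% to 65% belongs to 20/40. With the 40 recruited patients that the article fixes, a 50% rate has a denominator of 80 and a 95% interval of about 39% to 61%. The stated half-width of 15 points should be about 11. The error is conservative and minor: recruitment would be known better than claimed, not worse, and N = 40 and the retention interval are unaffected.

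The conclusion assumes that the recruitment rate is a proportion of patients with those recruited in the numerator, that the target of 40 is reached, and that an ordinary binomial interval is used. It does not depend on which standard interval is chosen, nor on whether the denominator is patients identified, eligible or approached. That the original calculation was a Wilson interval with n = 40 is inferred from its reproducing both printed intervals; the article does not name the method.

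**What to change.** Replace the sentence with wording such as: *With 40 randomised and a recruitment rate of 50%, the denominator will be about 80 patients, giving a 95% CI of about 39% to 61%; retention of 80% of the 40 randomised has a 95% CI of 65% to 90%.* The authors should add which group the 50% refers to (patients identified, eligible or approached). That choice is theirs, and the figure of 80 follows from any of them. If the interval method is named, it should be the same for both rates; with Wilson the recruitment interval is 39.3% to 60.7%.

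The cost is one reworded sentence. The sample size, the procedures and the planned descriptive analysis do not change.
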